#### COVID-19 Effect

Approximately 20% of patients during the trial will have received inpatient care either during or after the peak of the COVID-19 pandemic. The usual amount of fear and anxiety elicited by cardiac surgery and the associated recovery period enhance patients’ typical need for close physical, emotional, and psychological support from their loved ones. The hospital-wide policy prohibiting all visits during COVID-19 may cause an increase in the levels of fear and anxiety caused by surgery and recovery owing to enhanced feelings of isolation, separation, and possibly even abandonment—at such a crucial time of need—by the most important loved ones in their lives. These policy changes may enhance the impact of a comfort coach on the intervention arm, simply by adding more human contact through a caring and empathetic individual at these critical touchpoints of care, irrespective of the nonpharmacologic therapy the coach provided.

In contrast, the control patient group during the COVID-19 pandemic may be at a potential disadvantage compared with the control patient group before COVID-19 because the pre-COVID control group had the usual level of support from family, friends, and significant others. These 2 opposing effects, namely, a potential enhancement for the intervention group and additional tension and anxiety from isolation and separation among the control group, may have affected the study results. However, it is also possible that patients in the intervention group during COVID-19 remained anxious and fearful despite having a comfort coach because of separation from loved ones, fear of infection in the hospital, or other factors. Although we cannot mitigate the impact of COVID-19, we will perform a subset analysis of patients who received care during COVID-19 to evaluate for any significant differences in our data.

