### Patient Enrollment and Randomization

Cardiac surgical patients will be recruited from the Frankel Cardiovascular Center (FCVC) at Michigan Medicine. Opioid-naive patients undergoing first-time, elective cardiac surgery through a full median or miniature sternotomy beginning September 3, 2019, were screened for a targeted enrollment of 154 patients for randomization. Approximately 600 to 750 patients meeting these criteria underwent surgery at Michigan Medicine in 2017. Opioid-naive is defined as opioid-free at the time of preoperative clinic history and physical examination.

Patients lost to follow-up will be censored for data analysis, and missing individual intervention points will be dealt with by multiple imputations, as appropriate. We will compare the clinical and sociodemographic attributes of patients who decline participation and patients lost to follow-up with those of patients with complete follow-up to assess potential responder bias. We estimated a 20% rate of missingness, which was incorporated into our power calculation. On the basis of historical institutional data, we anticipated approaching 5 to 10 patients per week for potential enrollment, with an approximate 5 to 7 month enrollment period within a 12-month study period for completion of clinical follow-up, data analysis, and manuscript production. Although this timeline was affected by the COVID-19 pandemic forcing a pause in enrollment between March 14th and the time of writing, we were 93.5% (144/154) enrolled at the time of pausing and remained optimistic about completing enrollment within our 12-month study period. We used block randomization with randomly variable block sizes generated with Stata 15 software (StataCorp LLC, College Station, TX) and computer randomization occurred with the treatment assignment tool (Treatment Assignment Tool-University of Michigan [TATUM]) from the Michigan Institute for Clinical and Health Research.

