##### Power Analysis

Our primary endpoint is composite of health care utilization, defined as the total number of days spent at home within the first 30 days after surgery. Secondary endpoints include mean GAD-7 and PHQ-9, KCCQ-12, Picker Patient Experience Questionnaire, IES-R, and Brief Pain Inventory Scores and mean inpatient and outpatient opioid use.

We will compare mean days with a two-tailed *t* test and set the power of this study at 80% with alpha (Type I error) of .05 and the Cohen *d* effect size (defined as the difference in means divided by standard deviation) between medium (0.5) and large (0.8) [69,70], which yields a minimum sample size of 52 patients to detect a large effect size and 128 to detect a medium effect size [71]. Incorporating 20% missingness, a sample size of 154 patients will adequately detect a medium effect size. We next verified this statistically derived sample size with clinically relevant examples. Although most large series reporting opioid use report the median and interquartile range of OME [47,72], our sample size should be sufficient to satisfy the central limit theorem and use mean values. At our institution, the mean opioid use after sternotomy in 2017 was 200 OMEs. We estimated that to detect a 30% reduction in opioid use (mean 140 OMEs) with a standard deviation of 125 OME in the control and 100 OME in the intervention arms, a sample size of 114 would be required. For composite health care utilization, demonstrating a 3-day difference between the arms with a 6-day standard deviation would detect by a total sample size of 128 patients. With 154 patients, we should have adequate power to detect a difference in our primary outcomes for aims 1 and 2.

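### The COVID-19 question is about a change between periods, but the only analysis named is a significance search among COVID-period patients (about 31)

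*Protocol article*

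**What the plan says.** In the protocol article, Discussion, COVID-19 Effect, the plan expects that "Approximately 20% of patients during the trial will have received inpatient care either during or after the peak of the COVID-19 pandemic". It then gives reasons why the intervention might matter more in that period, why control patients might fare worse than control patients treated earlier, and why coached patients might stay anxious all the same. The analysis it commits to is: "we will perform a subset analysis of patients who received care during COVID-19 to evaluate for any significant differences in our data". That section names no comparison with the earlier patients and no arm-by-period term.

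The trial is sized only for the overall comparison. Under Power Analysis the plan will "set the power of this study at 80% with alpha (Type I error) of .05". For the primary endpoint it states that "demonstrating a 3-day difference between the arms with a 6-day standard deviation would detect by a total sample size of 128 patients", and it concludes: "Incorporating 20% missingness, a sample size of 154 patients will adequately detect a medium effect size".

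**The concern.** Whether the coach worked differently during COVID-19 is a question about the difference between two effects. Whether control patients did worse is a question about the difference between two control groups. Both need the pre-COVID patients in the analysis. A comparison of arms among COVID-period patients alone leaves them out and answers another question: is there an effect in this small group?

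The stated criterion, significant differences, makes this worse. A non-significant result in roughly 31 patients could be taken to mean that the pandemic removed the benefit, and a chance significant result could be taken to mean that it enhanced it. What is at stake is the conclusion about the pandemic, not the primary test.

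**Working it through.** **Inputs.** From Power Analysis: 154 patients, two-tailed t test, alpha 0.05, difference 3 days, SD 6 (d = 3/6 = 0.5). From COVID-19 Effect: a COVID share of about 20%. Assumed: 1:1 allocation (the ratio is not stated, but the plan's sample sizes reproduce under 1:1), equal SDs in both arms and periods, and no loss of patients unless noted.

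**The plan's own figure.** The noncentral t gives 63.8, so 64 per arm, or 128 in total, for d = 0.5. This agrees with the plan. Then 128 × 1.2 = 153.6, which gives 154.

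**Size of the two groups.** 0.20 × 154 = 30.8, about 31 in the COVID period. 154 − 30.8 = 123.2, about 123 before it.

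**Arm comparison inside the COVID subset.**
- SE = 6 × √(4/30.8) = 2.16 days.
- 95% CI half-width = 2.046 × 2.16 = 4.4 days (t with 28.8 df).
- Power at 3 days is 0.269, about 27% (26% with 15 per arm, 28% with 16 per arm).
- The smallest effect detectable with 80% power is d = 1.04, or 6.2 days.

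**Arm comparison in the remaining patients.** SE = 6 × √(4/123.2) = 1.08 days, and power at 3 days is 0.786, about 79%.

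**Chance that the two verdicts disagree when the true effect is 3 days in both periods.**
- Significant before but not during COVID: 0.786 × (1 − 0.269) = 0.575.
- Significant during but not before: 0.269 × (1 − 0.786) = 0.058.
- Total: 0.632, about 63%. A simulation of 200,000 trials gave the same.

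**Sensitivity.**

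| Setting | Disagreement |
|---|---|
| COVID share 10%, d = 0.5 | 73% |
| COVID share 20%, d = 0.5 | 63% |
| COVID share 30%, d = 0.5 | 55% |
| Share 20%, d = 0.5, 128 evaluable | 61% |
| Share 20%, d = 0 | about 10% |
| Share 20%, d = 0.3 | 41% |
| Share 20%, d = 0.8 | 43% |

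At a 20% share, disagreement exceeds 50% only for a true d between about 0.36 and 0.72.

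**The contrast that answers the question.** The SE of the arm-by-period interaction is √(2.16² + 1.08²) = 2.4 days, and its 95% CI half-width is 1.96 × 2.42 = 4.7 days. Power is about 24% for an interaction of 3 days. The smallest interaction detectable with 80% power is about 6.8 days (1.13 SD).

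**The case against.** Several counter-arguments have force.

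- **The sentence is loose.** It does not say that the test is arm against arm within the subset only. The same section mentions control patients before COVID-19, so a between-period comparison may be intended, and a fuller plan not shown here may spell it out. This stands as a limit: the power figures apply to the within-subset reading. The sentence still names only COVID-period patients and makes significance the criterion.
- **No rule compares verdicts across periods.** A reader might infer that the plan will test each period and contrast the two results, so that the trial will usually look discordant. The document does not support that. It plans no second test in the pre-COVID patients, and disagreement is the more likely outcome only for effects near the design value. The 63% shows what such a comparison would do if it were made.
- **The endpoint differs.** The section is mainly about fear and anxiety, while the day-based figures are for days at home. No SD is given for anxiety. The results carry over in SD units only, for a true d of 0.5.
- **The subset may not be 31.** The 20% refers to inpatient care during or after the peak. Patients with only follow-up in that period might also be counted, which would enlarge the subset. The 10% to 30% range covers part of this uncertainty.
- **Leaving period out of the primary comparison does no harm.** A reader might infer that the main result is biased by the pandemic. It is not: allocation was random, and the article states "We used block randomization with randomly variable block sizes", which keeps the arms roughly balanced over enrolment time. Period as a covariate is optional.
- **The replacement is also weak.** This is true. Its gain is that it estimates the right quantity and shows how uncertain that estimate is.

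**Conclusion.** The point holds in a limited form. The named analysis does not match the question the section raises and, read as an arm comparison in about 31 patients, is too small for its significance to carry meaning at the design effect. Discordance between periods would be common at that effect if verdicts were compared, but it is not a general property and not something the plan says it will look for. The conclusion rests on the plan's 20% share, 154 patients, d = 0.5, 1:1 allocation and equal SDs. Severity is minor: this is one exploratory analysis, and the primary endpoint and its test are untouched.

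**What to change.** Replace the subset sentence with text such as: *In an exploratory analysis of all randomised patients, we will fit arm, period (before or during/after the COVID-19 change, by date of surgery) and arm-by-period for days at home and for the anxiety outcomes. We will report the interaction and the period-specific effects with 95% confidence intervals. The interaction will be imprecise (for days at home, SE about 2.4 days; about 24% power for a 3-day interaction). No conclusion will be drawn from significance or non-significance in the COVID-period patients alone.*

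Fix the boundary date before the data are analysed. Surgery follows randomisation, so show the number of patients per arm in each period. A sensitivity version of the primary analysis with period as a covariate may be added but is not needed.

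The cost is one extra model with a wide interval. It needs no further patients and no new data, since the date of surgery is already needed to count the 30 days of the primary endpoint.

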### Conclusions

This clinical trial aims to evaluate the impact of a comfort coach administering nonpharmacological interventions on patient experience, opioid use, and health care utilization compared with usual care in adult cardiac surgery patients. Findings from this study may serve as the foundation for a subsequent multicenter trial, establishment of this role in the adult setting, and broader dissemination of these techniques to other types of surgery.

## Appendix

Multimedia Appendix 1 Supplemental material.

Multimedia Appendix 2 Peer Review Comments and Author Responses.

## Abbreviations

CABG: coronary artery bypass
FCVC: Frankel Cardiovascular Center
GAD-7: Generalized Anxiety Disorder 7-item scale
IES-R: Impact of Events Scale-Revised
KCCQ-12: Kansas City Cardiomyopathy Questionnaire short-form
OME: oral morphine equivalents
PHQ-9: Patient Health Questionnaire-9
TATUM: Treatment Assignment Tool-University of Michigan
